## 1. Introduction

The current healthcare system is facing a complex challenge, with rising costs and the need for improved quality of care [1]. This is exacerbated by the growing complexity of patient conditions, particularly chronic illnesses and an aging population, which put pressure on healthcare systems [2].

To maintain the sustainability of public finances, it is crucial to monitor public health expenditure. Governments reimburse health service expenditure through specific reimbursement systems, such as the Diagnosis-Related Group (DRG) system. The DRG system was created to maintain sustainable inpatient procedures, control healthcare costs, and categorize inpatients based on clinical and treatment criteria. Patients in the same group are expected to use similar resources, encouraging clinicians to effectively manage costs [3,4]. However, this system does not include the costs of nursing care [5].

Nurses are the largest professional group in the healthcare system. However, very little is known about the cost and quality of nursing care, and more specifically, the effectiveness of the care provided by each nurse [5]. In almost all countries, nursing care costs are considered a service cost and are included in the DRG system, similarly to hospitals’ other fixed costs [3]. The DRG system estimates the cost of hospital nursing care based on the total number of nurses assigned to inpatients. Consequently, nursing care costs are calculated as an average lump sum that does not take into account care intensity, the level of patient dependency, the variability in nursing resource consumption, and the intrinsic and intangible characteristics of nursing care [6]. This implies that the amount of nursing care may vary considerably even within the same DRG [7].

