## 2. Materials and Methods

### 2.1. Aims

The primary aims of this study are (1) to assess the variability of nursing costs between different DRGs and within the same DRG; and (2) to measure how much variability in the intensity of nursing care is explained by DRGs.

The secondary objectives of this study are (1) to measure the amount of nursing activity in acute care hospitals; (2) to examine the variability of the intensity of nursing care activities by DRG within patients and across patients controlling for hospital and region; and (3) to identify and quantify any differences in care needs among patients discharged with the same DRG.

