### 2.8. Data Analysis

Descriptive statistics (frequency, percentage, mean, median, range, and standard deviation) will be used to describe the sample. *t*-tests, ANOVA (or related nonparametric tests in case of a non-normal distribution of dependent variables), linear regression, and quantile regression will be performed to evaluate the possible variability in nursing time across hospitals and DRGs.

The chi-square test will be used to analyze any differences in the average frequency of nursing activities within the same DRG. In addition, we will perform linear, logistic and quantile regression, considering cost as the outcome of nursing care. Nursing costs will be assessed across hospitals and DRGs. The quantile regression will be used to explore which factors are associated with the different quantiles of nursing costs.

Nursing costs will be calculated based on several factors, including the average time required to perform each procedure, nurses’ hourly wage, the cost of materials used, and the average length of patient stay. Nursing time will be estimated using a convenience sample of nurses from the hospitals included in this study. For each nursing activity, the participating nurses will indicate the average time spent on the activity and devices relevant to each intervention. Nursing costs will be calculated by applying nurses’ salaries, based on national cost tables for nursing professionals. The annual nursing salary will be used to estimate the cost per minute of nursing time. This cost per minute will then be multiplied by the amount of time spent on each nursing activity and by the total number of activities performed for each patient. Additionally, the cost of devices required to perform each activity will be included, based on prices from the national price list. Thus, the cost per patient per day of hospitalization will be calculated. This cost will enable us to compare patients with different lengths of stay. Finally, subgroups based on patient complexity will be considered.

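### The labour cost formula in section 2.8 has no term for the number of nurses per activity, so two-nurse care may be under-costed by up to half and absolute within-DRG cost variability attenuated

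*Protocol article*

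**What the plan says.** Section 2.8 (Data Analysis) of the protocol article sets out the labour cost term by term.

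- Time: "For each nursing activity, the participating nurses will indicate the average time spent on the activity and devices relevant to each intervention". Earlier in the same section this input is described as the mean time a procedure takes.
- Price: "The annual nursing salary will be used to estimate the cost per minute of nursing time", with salaries taken from national cost tables for nursing professionals.
- Combination, with activities counted per patient: "This cost per minute will then be multiplied by the amount of time spent on each nursing activity and by the total number of activities".
- Devices are added separately from a national price list.

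Table 1 lists the number and type of nursing activities among the nursing record data. It has no field for how many staff performed an activity or in what role. Section 2.9 accepts that nurse-estimated times may over- or understate cost, depending on how accurately nurses report them. It does not mention the number of staff.

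The first primary aim (section 2.1) is "to assess the variability of nursing costs between different DRGs and within the same DRG". The Introduction faults current DRG costing because "nursing care costs are calculated as an average lump sum that does not take into account care intensity, the level of patient dependency" and other sources of variation.

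**The concern.** Salary is consumed per nurse, so the resource used by an activity is its duration times the number of nurses engaged. The formula multiplies duration by the number of occurrences only. A 5-minute repositioning done by two nurses uses 10 nurse-minutes but would enter as 5 if the surveyed time is elapsed time.

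This would not be a common scale factor that cancels in comparisons. Tasks such as turning or bed hygiene plausibly need two people mainly for dependent patients, whereas giving drugs or measuring vital signs does not. That clustering is an assumption; the article gives no data on it. If it holds, the costing loses part of the dependency-related variation that the Introduction says DRG costing ignores. The loss would reach the primary cost outcome, the complexity subgroups and the nursing case-mix analysis.

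**Working it through.** The plan states no figure for this point, so there is none to reproduce. What follows is algebra on the section 2.8 formula. All numerical inputs are assumptions.

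**1. Cost level.** Let T1 and T2 be a patient's elapsed minutes in one-nurse and two-nurse activities, c the cost per minute, and q = T2/(T1+T2).
- Formula cost = c(T1 + T2). Cost of the nurse time used = c(T1 + 2·T2). Ratio = 1/(1+q).
- q = 5%, 10%, 20%, 30%, 50% gives 0.95, 0.91, 0.83, 0.77, 0.67, a shortfall of about 5% to 33%.
- q = 100%, an activity always done by two nurses, gives 0.50. Device cost is unaffected.

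**2. What the ratio depends on.** The 0.50 needs elapsed time, one log entry per occurrence, and two nurses.
- Person-minutes reported for an always-two-nurse activity: ratio 1.00.
- Both nurses log the activity: ratio 1.00.
- Person-minutes averaged over mixed occurrences, a share p of them two-nurse: the single value is (1+p) times the duration. Two-nurse occurrences are costed at (1+p)/2 and one-nurse occurrences at 1+p. For p = 10% to 50% that is 0.55 to 0.75 and 1.10 to 1.50. The mean is right, but both kinds of occurrence carry the same cost.

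**3. Absolute within-DRG variability.**
- Formula: Var(T1) + Var(T2) + 2Cov(T1,T2). Nurse-minutes: Var(T1) + 4Var(T2) + 4Cov(T1,T2).
- Difference: 3Var(T2) + 2Cov(T1,T2), which is positive at zero or positive correlation.
- Grid: CV of T1 0.4, CV of T2 0.5 or 1.0, q 10% to 30%, correlation 0 or 0.5. The SD ratio (formula over nurse-minutes) is 0.62 to 0.97.
- Lower end (q = 30%, CV of T2 1.0, correlation 0, total 100 min): √[(28² + 30²)/(28² + 60²)] = √(1684/4384) = 0.62.
- Upper end (q = 10%, CV of T2 0.5, correlation 0): √[(36² + 5²)/(36² + 10²)] = √(1321/1396) = 0.97.
- At correlation −0.9 the sign can reverse: q = 20%, CV of T2 0.5 gives √(548/272) = 1.42.

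**4. Relative variability.** The mean shrinks as well. On the same grid at correlation 0 or 0.5 the CV ratio is 0.81 to 1.07, so it can move either way.

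**5. Share explained by DRG.** Suppose a dependent patient adds 6 × 5 + 25 = 55 elapsed two-nurse minutes a day, so the gap d to an independent patient is 55 by the formula and 110 in nurse-minutes. Take two equal-size DRGs with 20% and 50% dependent patients and residual SD s of 20 or 40 min.
- Between-DRG variance = (0.15d)²: 68.1 against 272.3.
- Within-DRG variance = 0.205d² + s², where 0.205 is the mean of 0.2 × 0.8 and 0.5 × 0.5. This is 1020 to 2220 against 2881 to 4081.
- Share: 3.0% to 6.3% by the formula against 6.3% to 8.6% in nurse-minutes. Here the formula understates the share.
- If the DRGs instead differ only in one-nurse time, between-DRG variance is the same under both costings while the within-DRG part is larger in nurse-minutes, so the formula overstates the share.

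**6. Role.** Add 100 one-nurse minutes to the same dependent patient. The formula gives 155.
- Two nurses: 210 nurse-minutes used, so the formula is 26% low.
- One nurse and one support worker, the latter kept out of nursing cost: 155, no error.
- Two support workers, likewise kept out: 100, so the formula is 55% high.

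**The case against.** The strongest reply is that the article does not define the surveyed time. Section 2.8 speaks of nursing time, which could mean nurse-minutes, and the questionnaire or full protocol may say so. The national cost tables may also separate staff grades. Two-person care is mentioned nowhere in the article, and section 2.9 already concedes possible over- and underestimation.

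Part of this stands. A reader might infer that two-person care is costed at half, that within-DRG variability is understated, and that the share explained by DRG is therefore overstated. The documents do not support any of these as flat statements. The first needs the three conditions in step 2, the second needs zero or positive correlation and holds for the absolute scale only, and the third can run the other way (step 5). The support-worker issue pulls cost in the opposite direction.

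The rest does not remove the point. The article goes beyond silence: it states the formula and says what nurses are asked, and duration is the natural reading of a procedure's mean time. Reading it as nurse-minutes still leaves one value per activity for all patients. Perfectly accurate elapsed times would carry the same error, so the training foreseen in section 2.9 would not cure it. Section 2.7 expects hospitals to organise activity data differently. If some log a two-nurse activity once and others twice, identical care would differ in labour cost by a factor of two between hospitals.

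**Conclusion.** The point holds in conditional form. The stated costing rule has no term for the number of nurses. With elapsed time and single logging, the labour cost of two-nurse activities is understated by up to half, and total patient labour cost by about 5% to 33% for an assumed two-nurse share of 5% to 50%. Absolute within-DRG variability is likely attenuated if two-nurse care clusters in dependent patients, with SD ratios of 0.62 to 0.97 on the assumed grid. No direction can be claimed for relative variability or for the share explained by DRG. The change is worth making because it protects the primary cost outcome at little expense; the documents do not show that the results must be biased in a known direction.

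**What to change.** In section 2.8:

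1. Define activity time as nurse-minutes.
2. Have the planned nurse questionnaire record, for each activity, the minutes, the usual number of nurses, and whether a nurse or a support worker usually performs it.
3. Use minutes × number of nurses in all time and cost analyses.
4. Keep support-worker minutes out of nursing cost, or cost them separately at their own rate.
5. Establish for each hospital whether its electronic record logs a two-nurse activity once or twice. Where each nurse logs it, do not apply the multiplier, since that would double count.
6. Use staff numbers that vary with patient dependency only in a sensitivity analysis. In the main costing they would build dependency into the cost that the complexity analyses then try to explain. Section 2.6 also takes complexity only at admission and before discharge, with tools that may differ between hospitals.

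The cost is one or two more questions per activity, a query to each hospital about logging, and one multiplier in the costing code. No new patient records are needed. If the time estimates have already been collected, the number and role of performers can be added per activity afterwards.

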### 2.5. Eligibility Criteria for Patients

All data regarding included patients admitted and discharged in the year 2022 will be collected. Data will be collected from patients who meet the following inclusion criteria: (a) patients with medical or surgical DRGs (selected by the department code on the hospital discharge form) with a length of stay > 1 day; (b) patients whose admission and discharge took place in the same ward; and (c) patients admitted and discharged in 2022. Patients aged < 18 years will be excluded.

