### 2.7. Procedures

This study started in January 2024 and is planned to end in March 2025. First, a pilot study was conducted to assess the characteristics of the EHR in the enrolled hospitals. Given the lack of a unique national electronic system for storing health information, heterogeneity in the collection and organization of the nursing activities is expected. Therefore, a preliminary meeting was organized with the nursing directors of each hospital. During this meeting, nursing directors described the EHR used in their hospitals. From this information, an electronic dataset was prepared to allow each hospital to enter information on nursing care activities. For each hospital, two medical and two surgical wards will be considered for enrolment. If there are more than two medical/surgical wards in the same department, the two wards with the highest number of patients admitted during the study period will be selected.

Eligible patients will be enrolled by searching the EHR. Data will be collected retrospectively to gather information on nursing care provided in 2022. This study will collect data from all patients included in medical or surgical DRGs. All nursing activities performed on these patients and documented in the EHR will be considered.

Within each hospital, a procedural manager will be designated to extract and de-identify data of interest. The data of patients who meet the inclusion criteria will be transmitted to the principal investigator (PI) by uploading the data into a secure server specific for this study. The upload will take place via a dedicated cloud platform established on an ad hoc basis for the project, allowing each local investigator of the participating centers to access and provide data.

For login purposes, each local investigator will have a username and password (which can be modified by the user after the initial login). Each local investigator will only have access to his or her own uploaded data, while the principal investigator will have access to all the data submitted by each participating center. The Italian Regulatory Board for Nursing Professions (FNOPI) owns the server where the data will be kept. Data gathering will be continuously evaluated, and all disaster recovery measures will be in place. Figure 1 summarizes the steps of the study.

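### Cost per day is presented as making stays of different length comparable, but any once-per-stay nursing care leaves it dependent on length of stay

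*Protocol article*

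**What the plan says.** Section 2.8 (Data Analysis) builds the cost of a stay from a cost per minute of nursing time, "multiplied by the amount of time spent on each nursing activity and by the total number of activities performed for each patient", plus the cost of devices. It continues: "Thus, the cost per patient per day of hospitalization will be calculated". The stated purpose follows: "This cost will enable us to compare patients with different lengths of stay".

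Section 2.7 (Procedures) sets what is counted: "All nursing activities performed on these patients and documented in the EHR will be considered". It makes no split between work done once per stay and work repeated daily.

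Section 2.5 admits medical and surgical cases "with a length of stay > 1 day" and states no upper limit. Earlier in section 2.8, the factors entering the cost include "the cost of materials used, and the average length of patient stay", so it is not fully clear whether the divisor is the patient's own days or an average.

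The second primary aim in section 2.1 is "to measure how much variability in the intensity of nursing care is explained by DRGs". The first concerns the variability of nursing costs between DRGs and within a DRG.

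**The concern.** Dividing by days removes the effect of length of stay only if nursing minutes are proportional to days. Some nursing work belongs to the stay and not to the day. Section 2.6 points to such work: nurses score care complexity at admission, and the last score before discharge is also taken. Surgical stays may add care around the operation.

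Where such work is in the numerator, the per-day value carries a term that shrinks as the stay lengthens. DRGs differ in length of stay, and stays also vary within a DRG, so the term enters both primary aims. Differences in mean stay add variance between DRGs, and the spread of stays adds variance within them. The Introduction foresees adjusting DRG cost weights or setting a nursing intensity weight for each DRG, so a reader could carry a length-of-stay effect into a payment recommendation as if it were daily nursing intensity.

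**Working it through.** The article states no figure that depends on this point, so there is none to reproduce. The check is algebra plus assumed values.

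**From the documents.** The numerator is all documented activities of the stay (2.7, 2.8). The measure is cost per patient per day (2.8). Stays exceed 1 day (2.5), taken here as 2 days at the shortest. The expected sample is at least 15,000 patients (2.9).

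**Assumed, because the documents give no value.** Daily care v = 100 minutes on every day. Once-per-stay care F = 0, 60, 120 or 180 minutes.

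**Formula.** Minutes per stay = F + vL. Minutes per day = (F + vL)/L = v + F/L. This is free of L only when F = 0. With a constant cost per minute, and devices left aside, cost behaves in the same way.

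| F (min) | 2 days | 5 days | 10 days | ratio 2:10 days | ratio 3:7 days |
|---|---|---|---|---|---|
| 0 | 100 | 100 | 100 | 1.00 | 1.00 |
| 60 | 130 | 112 | 106 | 130/106 = 1.23 | 120/108.6 = 1.11 |
| 120 | 160 | 124 | 112 | 160/112 = 1.43 | 140/117.1 = 1.20 |
| 180 | 190 | 136 | 118 | 190/118 = 1.61 | 160/125.7 = 1.27 |

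**When the ranking is masked.** A 10-day stay matches the per-day value of a 2-day stay if its daily care is v + F/2 − F/10. For F = 60 this is 100 + 30 − 6 = 124 minutes. For F = 120 it is 100 + 60 − 12 = 148, and for F = 180 it is 100 + 90 − 18 = 172. Above these values the order reverses.

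**Effect on the share explained by DRG.** A simulation used 15,000 patients in 50 DRGs with identical F and v, so that DRGs differed only in mean stay. Assumptions: median DRG mean of about 6 days, coefficient of variation of care 0.3, 20 runs. F is expressed in days' worth of routine care.

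| F (days' worth) | Per-day cost variance attributed to DRG | Correlation of DRG mean cost per day with DRG mean stay |
|---|---|---|
| 0 | 0.3% (chance level) | −0.07 |
| 0.5 | 1.7% | −0.83 |
| 1 | 4.8% | −0.90 |
| 2 | 11.4% | −0.90 |

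**If the divisor were the average stay.** Dividing each stay's cost by the overall mean stay reverses the direction: DRGs with longer stays look costlier. In the same simulation DRG then accounted for about 23% to 25% of the variance, even with F = 0. The value is again not independent of length of stay.

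**The case against.** The strongest reply is that cost per day is a recognised scale and that the article never calls it adjusted for length of stay. The Introduction cites a per-diem nursing-intensity model. A patient whose care is concentrated around surgery does use more nursing per day, and for an aim about intensity that may be signal. This stands: cost per day is a valid measure of average daily workload. What fails is the unqualified statement that it makes stays of different length comparable.

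The reply continues that the regressions of nursing time and cost may include length of stay, which section 2.2 lists among the extracted data, and that covariates are commonly left to an analysis plan. This also stands. It cannot be inferred that the final analysis will ignore length of stay. The text does not say whether the modelled cost is per stay or per day, and the sentence needs correcting either way.

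A reader might infer that short-stay DRGs will necessarily be reported as more nursing-intensive. The documents do not support that. It needs F above zero, equal daily care and the patient's own days as divisor. They give no activity list, no value of F and no distribution of stays, and the divisor is ambiguous.

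Finally, adjustment has its own problem. Length of stay is partly determined by DRG and severity, so comparing DRGs only at a common length of stay can remove real differences. This is a good reason to show adjusted results beside unadjusted ones and not to replace them.

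**Conclusion.** The point holds as a correction to a stated claim. Section 2.8 credits cost per day with a property it has only if no counted care is tied to the stay, and sections 2.7 and 2.8 count everything documented. Neither the bias section (2.9) nor the limitations (section 3) mentions this.

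The size cannot be taken from the documents. In the assumed range of 60 to 180 minutes the apparent excess is 23% to 61% for 2 versus 10 days, and 11% to 27% for 3 versus 7 days. In the simulation, the variance attributed to DRG without any difference in F or v was modest at small F and reached 11.4% at F equal to two days of care. The net direction in real data is open. The stronger conclusion, that the measure is invalid or that the DRG ranking will be wrong, does not follow.

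**What to change.** In section 2.8:

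1. Replace the comparability sentence with a statement that cost per day describes average daily workload and is not independent of length of stay.
2. State that the divisor is the patient's own days of stay, and clarify what the average length of stay is used for.
3. Report nursing time and cost per stay beside cost per day for each DRG.
4. Add one companion analysis for primary aims 1 and 2. Either model cost per stay on length of stay and DRG, with a slope that may differ by DRG, or report once-per-stay activities separately from daily ones. The two options are related but not equivalent: a regression intercept is not the same quantity as the summed cost of flagged activities. A single common slope would assume the same daily cost in every DRG, which is the quantity under study.
5. Show results adjusted for length of stay next to unadjusted ones.

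No new data are needed. Length of stay is among the extracted data (2.2), and Table 1 lists admission and discharge dates and activity type. The cost is a slightly less simple headline measure and a little more analysis. The activity split also requires the once-per-stay activities to be classified, preferably before the costs are examined.

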### 2.6. Study Variables

The variables that will be collected are listed in Table 1.

Comorbidity will be assessed using the Cumulative Illness Rating Scale (CIRS), a validated tool used for hospitalized geriatric patients [14]. The disease severity score, ranging from 0 to 4, is based on 14 components reflecting organs impacted by a chronic disease. The CIRS Severity Index measures the number of items with disease severity ratings of three or four. This index is measured on hospital discharge forms at a national level.

To assess the complexity of patients, the score of the Corridor Triage (Tri-Co) instrument will be collected. Tri-Co is composed of the Modified Early Warning Score (MEWS) [15] and the Index of Care Dependency (IDA) [16]. The first tool collects data on clinical stability/instability, while the second one classifies information on care complexity. The integration of those two instruments is justified by the concept that clinical instability and care complexity should naturally complement each other to correctly classify patients according to their level of care intensity and ensure that the provision of care is proportional to the patient’s clinical complexity [17]. Tri-Co has been previously evaluated in several Italian settings [18,19,20]. If Tri-Co is not used in the hospital or wards included in this study, considering the expected heterogeneity in care complexity assessment among hospitals, other validated tools for measuring complexity will be considered. For example, the National Early Warning Score (NEWS), the Index of Care Intensity (IIA), or the Index of Care Complexity (ICA) may be considered [20]. All these measures will be collected as single measures at the beginning and at the end of the patient’s stay and specifically at the time of patient’s admission and the last measurement before discharge, as these assessments are made by nurses to ensure adequate nursing planning.

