Moreover, nursing costs will also be compared between patients with chronic and acute diseases. This will allow us to explore the hidden nursing costs derived from the nursing care delivered on an ongoing basis for chronic diseases (e.g., symptom monitoring, administration of medication for the chronic disease, etc.) that did not show signs of exacerbation during hospitalization. A subgroup analysis will be considered to determine which patients require more nursing care (in terms of time and costs). The nursing case mix (i.e., the patient characteristics that best explain the amount and costs of nursing care) will be evaluated to provide evidence for separating out nursing care activities and nursing intensity in the Italian prospective payment system.

To enable accurate data analysis, the need to normalize scores obtained from different rating scales measuring the same outcome will be evaluated. If information from the retrieved nursing records is missing, a missing value analysis will be performed to assess the appropriateness of multiple imputation [21]. Specifically, the reason for missingness will be examined, followed by the analysis of fraction of missing information and assessment of auxiliary variables to be used for multiple imputation. Then, sensitivity analyses involving several imputation models may be performed based on missing value analysis. Patients with missing data from all variables retrieved from the nursing record (i.e., missing data on nursing activities, nursing assessment and patient complexity) will be excluded. All descriptive and inferential analyses will be performed using R V. 4.4.2 [22] or similar software. The level of significance for all analyses will be fixed at *p* < 0.05.

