## Figures and Tables

**Figure 1 healthcare-13-00167-f001:**
[figure not shown]
Study phases.

**Table 1 healthcare-13-00167-t001:** Variables that will be collected divided by data source.

Hospital discharge data	Patient sociodemographic characteristics
	Date of patient admission
	Date of patient discharge
	DRG^†^ number assigned for each admission
	MDC number related to assigned DRG
	Admission diagnosis ^$^
	Discharge diagnosis ^$^
	1st secondary diagnosis ^$^
	CIRS
Nursing record data	Number of nursing activities performed for the same DRG
	Type of nursing activities
	Patient-related care complexity *
	Nursing assessment ^§^

DRG^†^: Diagnosis-Related Group; MDC: Major Diagnostic Category; ^$^: based on the *International Classification of Diseases*, 9th Revision, Clinical Modification (ICD-9-CM); CIRS: Cumulative Illness Rating Scale; ^§^: intended as the assessment carried out on the patient through the use of rating scales according to the company organization; *: care complexity will be measured by means of a validated tool used by hospitals.

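### The chronic-versus-acute cost comparison in section 2.8 does not isolate the nursing cost of background chronic disease that it is meant to explore

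*Protocol article*

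**What the plan says.** In the protocol article, section 2.8 (Data Analysis) states the contrast: "nursing costs will also be compared between patients with chronic and acute diseases". The next sentence gives its purpose: "This will allow us to explore the hidden nursing costs derived from the nursing care delivered on an ongoing basis for chronic diseases". The same sentence limits the diseases of interest to those "that did not show signs of exacerbation during hospitalization".

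Other parts of the article bear on this:

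- Section 2.1 (Aims) sets the first primary aim as "to assess the variability of nursing costs between different DRGs and within the same DRG". The chronic/acute comparison is neither a primary aim nor a secondary objective.
- Section 2.5 admits "patients with medical or surgical DRGs (selected by the department code on the hospital discharge form) with a length of stay > 1 day". No criterion there separates chronic from acute patients.
- Table 1 lists the DRG, the admission and discharge diagnoses, the "1st secondary diagnosis" and CIRS. It lists no variable for exacerbation.
- Section 2.6 says that the CIRS score "is based on 14 components reflecting organs impacted by a chronic disease", and that "The CIRS Severity Index measures the number of items with disease severity ratings of three or four".
- Section 2.8 puts cost on a per-day scale so that stays of different length can be compared. It also names regressions with cost as outcome, but gives no covariates and does not link them to this contrast.

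**The concern.** The target and the contrast stand in adjacent sentences and do not match. The target is what a background chronic disease adds to nursing cost when it is not itself causing trouble. Finding it calls for patients with such a disease to be compared with otherwise similar patients without it. The plan instead compares patients who have chronic disease with patients who have acute disease.

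Two problems follow from that choice. First, the patient of interest usually has both, so part of the cost sought sits in the comparator. Second, chronic and acute patients come to hospital for different reasons and so fall into different DRGs, whose nursing costs may differ for reasons unrelated to background chronic disease. A third problem is conditional: stays for worsened chronic disease may enter the chronic group, unless the non-exacerbation clause is meant as a rule for forming it.

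At stake is the reading of one exploratory result. A difference in case mix could be reported as the hidden nursing cost of chronic disease.

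**Working it through.** The article attaches no figure to this analysis, so there is nothing to reproduce. The check is to write down what the contrast estimates and see when it equals the target.

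**Quantities.** All values below are assumed; none comes from the documents.

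- h: true added nursing cost per day of quiet chronic disease, set to 1.
- p: share of the acute group that also has quiet chronic disease.
- q: share of the chronic group whose disease was exacerbated, with added cost e × h in place of h.
- D: difference in cost per day due to DRG mix, chronic minus acute, in units of h.

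**Formula.** Expected chronic-minus-acute difference = h(1 − q) + q·e·h + D − p·h.

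In general this equals h only if p = 0, D = 0, and either q = 0 or e = 1. Otherwise it equals h only where biases happen to cancel.

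**One source at a time (true value 1).**

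| Source | Setting | Contrast |
|---|---|---|
| Overlap | p = 0.3 | 1 − 0.3 = 0.7 |
| Overlap | p = 0.6 | 1 − 0.6 = 0.4 |
| DRG mix | D = −1 | 1 − 1 = 0 |
| DRG mix | D = +1 | 1 + 1 = 2 |
| Exacerbation | q = 0.3, e = 2 | 0.7 + 0.6 = 1.3 |
| Exacerbation | q = 0.6, e = 3 | 0.4 + 1.8 = 2.2 |

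**Non-exacerbation clause read as a group rule (q = 0).** The contrast becomes 1 − p + D. For p from 0 to 0.6 and D from −1 to +1 it runs from 1 − 0.6 − 1 = −0.6 to 1 − 0 + 1 = 2. The mismatch therefore does not depend on exacerbated stays.

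**All sources together.** With p and q in {0, 0.3, 0.6}, e in {1, 2, 3} and D in {−1, 0, 1}, there are 81 settings. The contrast runs from −0.6 to 3.2, and 9 settings lie within 10% of the true value. Five of these have no bias (p = 0, D = 0, and q = 0 or e = 1); in the other four, biases offset each other.

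**Would sharper definitions of chronic and acute suffice?** Suppose the groups are made mutually exclusive and exacerbated stays are left out. If patients with both kinds of disease go to the chronic group, then p = 0 and the contrast is h + D, so the DRG mix remains. If they go to the acute group, the cost sought lies in the comparator. The comparator itself has to change.

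**What the planned provisions cover.** Cost per day deals with length of stay and leaves D untouched. Control for hospital and region is stated in section 2.1 for a different objective. The expected sample of at least 15,000 (section 2.9) narrows the interval around the contrast but does not move it towards h.

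**The case against.** The strongest reply is that the article condenses a fuller plan, and that group definitions and covariates for an exploratory comparison may properly be left to that plan. That is fair as far as definitions go. It does not remove the point, because the article names the comparator and says that it will serve the purpose, and tighter definitions of the same two groups would not make it do so.

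Four stronger readings are tempting, and the documents do not support them:

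- *That the chronic group certainly contains exacerbated stays.* The clause "that did not show signs of exacerbation during hospitalization" can be read as restricting the group. On that reading this part of the concern disappears, while overlap and DRG mix remain.
- *That the comparison is fixed as a crude one.* The article does not say so. Regressions on cost and within-DRG aims are planned; they are simply not tied to this contrast.
- *That the result will have the wrong sign.* A reader could build such a case. Assume 60 euro/day for exacerbation stays, 80 for other acute stays, and a true addition of 10. A half-and-half chronic group averages 0.5 × 60 + 0.5 × 90 = 75, which is 5 below the acute group. These figures are invented, and the reversal comes only from the exacerbated half: without it the difference is 90 − 80 = +10. The article gives no costs from which a sign could be predicted.
- *That this contrast is to be the evidence for changing the payment system.* Section 2.8 states that purpose for the nursing case-mix analysis. For this comparison it claims only exploration.

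**Conclusion.** The point holds in a limited form. Comparing patients with chronic and acute diseases does not isolate the nursing cost of chronic disease that stayed quiet, because the groups overlap in the very patients of interest and because the split is confounded with DRG. Mixing with exacerbated stays is a further possibility that depends on how one clause is read.

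The overlap rests on the inference that, in an acute hospital, a patient with quiet chronic disease usually has another reason for admission. The confounding rests on DRGs being assigned on clinical grounds and treatment (Abstract), and on the study's own premise that nursing cost may vary between DRGs.

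The size cannot be derived from the documents. The assumed values show only that the contrast can fall well below or above the true cost. Severity is minor to moderate: the analysis is exploratory, is not a listed aim, and does not touch the primary results.

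**What to change.** Replace the comparison in section 2.8 as follows:

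- **Contrast.** Compare cost per day between patients with and without a background chronic condition that is not the principal discharge diagnosis. Make the comparison within the same DRG (stratified, or with DRG as a regression term) and adjust for age and hospital.
- **Separate group.** Report stays with the chronic disease as principal discharge diagnosis on their own, outside this contrast.
- **Classification.** Identify background chronic disease from the first secondary diagnosis together with CIRS, or from all coded secondary diagnoses if the discharge record can supply them. The first secondary diagnosis alone cannot show that a patient has no chronic condition. CIRS helps most if item scores are available, since the Severity Index counts only items rated three or four.
- **Wording of the result.** Describe it as the within-DRG difference associated with background chronic disease. State that diagnosis position is only a proxy for non-exacerbation: a secondary chronic disease can worsen during a stay, and a principal one can be stable.
- **Stated limitation.** Missed chronic conditions would probably pull the difference towards zero. If a share m of the group classed as without chronic disease in fact has it, at the same added cost h, the difference is h(1 − m); an assumed m of 0.3 gives 0.7 for a true value of 1.

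The cost is one rewritten paragraph, mostly using variables already planned, plus a request for item-level CIRS or further secondary diagnoses where the records hold them. DRGs with few patients in one of the two groups will contribute little, and some misclassification will remain.
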